#### Statistical analyses of secondary outcomes

We will perform several additional analyses of the secondary parameters. When appropriate, we will perform *t*-tests for continuous variables, or regression analysis with adjustment for prognostic baseline variables to increase efficiency and account for suspected confounding. For continuous variables (disease burden, and depression and anxiety scores, for example) measured several times during follow-up and probably missing data of some patients at some time points, longitudinal effects of the treatment strategies will be assessed with linear mixed models. For dichotomous variables, we will calculate differences in risks with a 95% confidence interval and compare the two treatment arms with the use of a chi-square test. Repeated measurements of dichotomous variables will be analysed with generalised estimating equations (if needed with reweighting for missing data) and logistic regression mixed models.

##### Combining the results of the different trials

Since the design of the three RCTs is similar, with the main difference being the duration of DA pre-treatment, the main results will be compared between the three RCTs and the PRolaCT-O study. We first compare the baseline characteristics between the studies. Then, a combined analysis including PRolaCT-O and the RCTs will be performed, using meta-analysis methods. If the results of the different studies differ substantially, we will explore if the differences can be explained by different patient populations in the different studies, using individual patient data (IPD) meta-regression methods, combined with inverse probability weighting.

Moreover, we will compare surgical outcomes between the intervention groups of the three RCTs, using a multivariate analysis, to compare the effects of the duration of DA pre-treatment on surgical outcomes.

In addition to the aforementioned analyses that will be performed according to the intention-to-treat principle, we will perform per-protocol analyses for both our primary and secondary endpoints.

### Economic analysis

#### Cost-effectiveness analysis (CEA)

The economic evaluation will consist of both trial-based cost-effectiveness analyses for all three RCTs and PRolaCT-O (costs per additional patient in remission and cost per quality-of-life adjusted life-year (QALY)) using observed cost and outcome data, and a model-based cost-utility analysis with a lifetime horizon (costs per QALY), in which all different treatment options are compared. In the trial-based economic evaluations, the effects of surgical treatment for patients with prolactinomas will be compared to standard care and related to the difference in costs. Differences in mean costs and effects between strategies will be compared with two-sided bootstrapping. In a net-benefit analysis, costs will be related to the outcomes and presented in a cost-effectiveness acceptability curve. No discounting will be applied due to the short time horizon of the economic evaluation. The evaluation will be performed from a societal perspective. Sensitivity analyses will be carried out for the most important assumptions.

In the model-based cost-utility analysis, a decision tree model will be used to extrapolate the trial results to lifetime costs and QALYs for different surgical treatment options (with and without pre-treatment with cabergoline) in comparison with usual care [29, 30]. In this lifetime cost-utility analysis, costs will be discounted at a percentage of 4% and effects at a percentage of 1.5%, according to the Dutch guidelines for health economic research [34]. Sensitivity analysis will be carried out for the most important input parameters.

Health care use and absence from work will be assessed with the iMCQ and iPCQ. For the valuation of health care, standard prices published in the Dutch costing guidelines will be used [35]. Costs of absenteeism from paid work will be calculated using the friction cost method. QALYs will be estimated with aid of the EQ-5D-5L. Utilities will be calculated from the EQ-5D-5L questionnaire using the Dutch tariff [36]. Using the area-under-the-curve method for the utility scores obtained for each participant, the QALY outcome per participant will be obtained for the trial-based cost-effectiveness analysis. Furthermore, utility values will be used as input in the model for the lifetime cost-effectiveness analysis.

### Data collection

During the study, all study data will be collected and stored in the data management system Castor EDC, with the use of an electronic case record form (eCRF), secured with personal login codes. Participants will be assigned a unique subject number. All data will be collected, stored, and analysed in a coded manner and in accordance with the General Data Protection Regulation (GDPR). The key to subjects’ identification codes will be stored securely at the study site, separate from all other study-related data. After the study ends, all exports of the study data and eCRFs will be stored digitally on the hospital server of the LUMC in a protected folder with access limited to the principal and coordinating investigators of the LUMC. Study data will be stored for 10 years after the study ends. There will be no collection or storing of biological specimens for this study.

### Safety reporting

For the RCTs, any adverse event (AE) that may occur in the standard care groups or the intervention groups after patients are referred back to their own hospital is either an expected result from standard care (and thus measured as part of the study outcomes) or not at all related to the prolactinoma or the received treatment. It is thus highly unlikely that any AE occurring in these patients is related to study participation. AEs will therefore only be recorded for participants in the intervention groups, when they are treated and under medical follow-up in the participating neurosurgical expertise centres. Furthermore, all observed or patient-reported adverse events will be recorded, unless there is a clear relation to pregnancy, e.g. nausea due to morning sickness. All AEs will be followed until they have abated, or until a stable situation has been reached.

All AEs are part of the safety data discussed with the Data Safety Monitoring Board. Moreover, the MREC is notified of all AEs that either result in death, are life-threatening, require non-elective hospitalisation or prolongation of hospitalisation to a maximum of 10 days in case of hospitalisation for prolactinoma surgery, result in persistent or significant disability or incapacity, or are a congenital anomaly or birth defect.

AEs that may occur in participants in PRolaCT-O will not be recorded, because the observational nature of their participation will imply that any AE will not be related to study participation.

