## Background

Prolactin-producing pituitary adenomas typically cause functional hyperprolactinaemia, which is characterised by galactorrhoea and hypogonadism, and may therefore result in subfertility [1]. Additionally, non-specific symptoms, such as fatigue, and psychological and neurocognitive complaints have been described [1]. Although a rare condition, prolactinomas account for over half (32–66%) of all pituitary adenomas [1]. Prolactinomas are found 3 times more frequent in women than in men with a peak incidence between the age of 25 and 35 years [2, 3]. The majority of prolactinomas are subcategorised, based on the size on magnetic resonance imaging (MRI), as microprolactinomas (< 10 mm; 80%), but they may also present as macro (10–40 mm) or giant (> 40 mm) and invasive tumours, which may compromise visual function due to compression of the optic chiasm, nerves, or tracts [2].

Prolactinoma treatment is primarily targeted at reduction of symptoms and restoration of gonadal status and fertility by normalising prolactin levels [4]. As it is a highly effective and non-invasive treatment option, medical treatment with a dopamine agonist (DA) is recommended as first-line treatment for almost all prolactinoma patients, while endoscopic transsphenoidal resection is reserved for those patients with (severe) DA intolerance or in case of DA-resistant prolactinoma [4].

Although DA treatment results in normalisation of prolactin levels, and subsequent reduction of symptoms in 81% of patients, the 2-year remission rate after DA withdrawal remains low (34%) and, therefore, long-term medical treatment should be expected [5]. DA treatment is usually well tolerated, although orthostatic hypotension and gastrointestinal complaints are frequently reported as side effects. DAs are furthermore associated with psychological side effects, which are mild in 40%, but more severe in up to 5–10% of patients [5–13]. Particularly, impulse control disorders (ICDs), e.g. pathologic gambling, are acknowledged as a typical side effect [13–16]. The heterogenous pattern of side effects and prolactinoma symptomatology may (in part) explain that both untreated (symptomatic) and medically treated prolactinoma patients have reported a decreased physical and mental health-related quality of life (HRQoL) [5, 17–22].

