#### Control: standard care

All participants who are randomised for standard care will receive treatment as usual from their own endocrinologist or gynaecologist as described by the US Endocrine Society [4].

First-line treatment is with DA, of which cabergoline is used most often; alternatives are bromocriptine and quinagolide. The dosage is usually titrated to achieve a normal or suppressed prolactin level in combination with restoration of the gonadal axis. DA treatment is discontinued after 2 years of treatment, i.e. 24 months after randomisation, unless a normal prolactin level cannot be achieved, and is restarted when prolactin levels rise after the medication is discontinued. As is customary in standard care, patients in the control group may be offered surgery in case of DA intolerance (side effects) or an insufficient response to DA treatment.

All participants may use any form of co-medication when medically indicated. Surgery is not performed on a pregnant participant, unless specifically indicated. Women who are pregnant at the time of randomisation are therefore not eligible for inclusion in an RCT. If a patient enrolled in one of the RCTs becomes pregnant after randomisation, she will remain in the trial, but treatment will be adapted, according to standard clinical care.

Our intervention protocol has been conceived in agreement with current standards of care for prolactinoma patients with an indication for surgery. Therefore, there are no specific strategies to improve adherence to intervention protocols. However, as part of the outcome data, we do monitor which treatment, surgical or medical, participants receive.

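### The pregnancy exemption from adverse event recording has no severity limit and, read literally, conflicts with the birth-defect criterion for ethics committee notification

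*Protocol article*

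**What the plan says.** All of the safety rules at issue stand in the Safety reporting section of the protocol article.

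- **Who is covered.** "AEs will therefore only be recorded for participants in the intervention groups", and then only while they are treated and followed in the neurosurgical expertise centres. For the observational cohort, "AEs that may occur in participants in PRolaCT-O will not be recorded".
- **What is recorded.** Within that group, "all observed or patient-reported adverse events will be recorded, unless there is a clear relation to pregnancy, e.g. nausea due to morning sickness".
- **What goes to the DSMB.** All adverse events form part of the safety data that it discusses.
- **What is notified.** "Moreover, the MREC is notified of all AEs that either result in death, are life-threatening". The list continues with unplanned or prolonged hospital stay and ends with events that "result in persistent or significant disability or incapacity, or are a congenital anomaly or birth defect".

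Pregnancy is foreseeable in this trial. Under Background, "Prolactinoma treatment is primarily targeted at reduction of symptoms and restoration of gonadal status and fertility by normalising prolactin levels"; the same section describes a threefold female excess and a peak incidence between 25 and 35 years. Under Control: standard care, "If a patient enrolled in one of the RCTs becomes pregnant after randomisation, she will remain in the trial", with treatment adapted. Pregnancy also enters the definitions of remission and of biochemical control at 12 months.

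**The concern.** A birth defect arises from a pregnancy, and so does a serious obstetric event. If an event clearly related to pregnancy is not recorded, a site that follows the recording rule as written has no record of it to pass to the DSMB, and the next paragraph's duty to notify the MREC has nothing to work from. The same applies to a life-threatening obstetric complication or an unplanned obstetric admission, each of which otherwise meets a listed criterion.

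What is at stake is whether the protocol's own serious-event criteria work for a foreseeable group of participants. Recruitment runs from five reference centres with regional networks, so different sites may settle the ambiguity differently. Safety data on pregnancies in the intervention groups would then be incomplete in a way that the DSMB could not see.

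**Working it through.** The plan states no figure on this point, so there is nothing to reproduce. The check has two parts.

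**1. The rules set side by side**

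| Event in an intervention-group woman under expertise-centre follow-up | Recording rule, read literally | Notification rule |
|---|---|---|
| Morning sickness | Exempt | Meets no criterion |
| Life-threatening obstetric event | Exempt | Notifiable |
| Unplanned obstetric admission | Exempt | Notifiable |
| Congenital anomaly in the child | Exempt | Notifiable |

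The rules agree in the first row and conflict in the other three. The morning-sickness example illustrates the exemption but does not bound it, and there is no exception for serious events or for the infant.

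**2. How many women the exemption can reach**

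Inputs:
- Planned size: 110 per arm in each RCT (Sample size calculation).
- Female share: 3 women to 1 man (Background), so 3/4 = 0.75. This describes prolactinoma in general, and its use for the enrolled patients is an assumption.
- Share conceiving during follow-up: not given in the document. I take 5–15% as an illustrative range.

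Three full RCTs, intervention arms only:
- Participants: 3 × 110 = 330.
- Women: 0.75 × 330 = 247.5, about 248.
- Pregnancies: 0.05 × 247.5 = 12.4 to 0.15 × 247.5 = 37.1, about 12–37.

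The RCTs combined to 220 participants in total, which the Sample size calculation section allows if recruitment proves difficult:
- Intervention participants: 110.
- Women: 0.75 × 110 = 82.5, about 83.
- Pregnancies: 0.05 × 82.5 = 4.1 to 0.15 × 82.5 = 12.4, about 4–12.

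Both results are upper figures at the stated rates. Women referred back to their own hospital leave adverse event recording for a different reason, and only a fraction of pregnancies would involve a serious event. The documents give no basis for estimating that fraction.

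**The case against.** The strongest reply is that the intent is plain. The only example is an ordinary pregnancy complaint, and naming birth defects as notifiable one paragraph later suggests that the authors did not mean to exclude them. A clear relation to pregnancy can also be read as meaning explained by the pregnancy alone, which need not cover an anomaly after possible drug exposure. Moreover, the notification sentence speaks of all adverse events, not of recorded ones. This stands to the extent that a reader who infers that the birth-defect criterion can never operate goes too far. It does not remove the conflict, because sites apply the recording rule as written and an event that is not captured is unlikely to be reported.

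Three other inferences are tempting, and the document does not support them:

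- *A lost or affected pregnancy would appear only as a treatment success.* The pregnancy route to remission requires conception during at least 3 months off dopamine agonist, so a woman who conceives on the drug does not qualify by it. Biochemical control counts a pregnancy that is present at 12 months, so one already lost does not count by that route.
- *The exemption hides pregnancies in both arms.* On the same assumptions, both arms of three full RCTs would give 0.75 × 660 = 495 women and about 25–74 pregnancies. Half of these are in the control arms, where adverse events go unrecorded whatever the pregnancy wording.
- *The trial fails to collect pregnancy outcomes.* The article registers pregnancy at visits. Details of how it ended may sit in the full protocol or case record form, neither of which is shown, so their absence from the article is not a finding.

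**Conclusion.** The point holds as a conflict between two stated rules. The exemption is unbounded and, on a literal reading, removes serious obstetric events and birth defects from recording and DSMB review, which weakens the notification duty for the only group whose adverse events are recorded. The group is at most about 248 women, with about 12–37 pregnancies over three full RCTs, or about 83 women and 4–12 pregnancies with a combined sample of 220. These counts rest on a 75% female share and an assumed 5–15% conceiving. The conflict itself depends on neither.

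The conclusion goes no further. It does not show that the criterion is inoperative, and it does not question the restriction of recording to the intervention groups, for which the section gives its own reasons. The gap is small in numbers and easily closed, and the wording should be changed.

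**What to change.** Reconcile the two sentences in Safety reporting:

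1. Limit the exemption to expected, non-serious symptoms of pregnancy.
2. State that any pregnancy-related event meeting one of the listed notification criteria is recorded, given to the DSMB and notified to the MREC.

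This can be done within the existing scope of recording and changes reporting only, not treatment. It costs one clause in the protocol and its communication to sites. The downside is a few additional reports.

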### Monitoring

#### Data Safety Monitoring Board (DSMB)

An independent DSMB will perform ongoing safety surveillance for the RCTs. The main responsibility of the DSMB for this study is guarding participant safety. Although complications related to the intervention are uncommon, this is the main interest for the DSMB. No formal interim analyses will be performed.

Monitoring of trial conduct and integrity will be executed every 6 months by internal monitors of the LUMC.

## Ethics and dissemination

The research protocol for the PRolaCT study has been reviewed and approved by the Medical Research Ethics Committee (MREC) of the LUMC and, when appropriate, by the local Institutional Research Boards (IRBs) of all participating centres. There is no formal steering committee or endpoint adjudication committee. However, there is an advisory board consisting of the principal investigators from St. Antonius Ziekenhuis, Medisch Spectrum Twente, and Radboud University Medical Centre, and our patient representative, chair of the Dutch Pituitary Foundation. The advisory board has been consulted during the development phase of the study protocol and is consulted for important protocol modifications. In addition, important protocol modifications are discussed with the DSMB and reviewed by the MREC of the LUMC, as is required by Dutch law on Medical Research involving Human Participants. After MREC approval, all principal investigators, and when deemed appropriate by the MREC, all participants, and the local IRBs will be notified, and the trial registry will be updated. Important protocol modifications will be declared transparently in the publication of the primary results.

Standard of care, which is primarily assessed in this study, is being covered by regular patient insurance. Damages to research participants through injury or death caused by the study will be reimbursed through a standard insurance for research participants, which covers the damage that becomes apparent during the study, or within 4 years after the end of the study. The risk of injury or death due to study interventions, which is neurosurgical counselling, is virtually non-existent.

After completion of the trials, the primary results of the RCTs will be unreservedly published in an open access and peer-reviewed journal.

## Discussion

### Rationale for the study design

Prolonged DA treatment for prolactinoma, which is current standard practice [1, 4, 5], is very effective in controlling hyperprolactinaemia and restoring gonadal function. However, patients may suffer from substantial side effects compromising HRQoL to a greater extent than previously described, while remission rates following DA treatment are lower than previously thought [5–13, 18–22, 37]. Although there is a low risk of complications, surgical resection induces swift disease remission in most patients, which may allow a drug-free future [5, 17, 23–26, 28, 38–46] with improved or even normalised HRQoL, and may thus deserve a more prominent place in the treatment of prolactinoma patients. However, loss of pituitary function and life-threatening complications must be considered.

The PRolaCT studies combine three randomised clinical trials and an observational cohort and are designed to compare both treatment strategies for patient-relevant outcomes, such as disease remission and HRQoL. For the RCT parts of PRolaCT, patients consent to randomisation between surgical counselling or standard care. If we would randomise between surgery versus DA treatment, all patients would have had to be referred to a neurosurgical expertise centre for surgical counselling prior to entering the study. With our pragmatic RCT design, only patients who randomise for surgical counselling are referred to the regional MDT to receive detailed information about surgical treatment for prolactinoma and standard care is delivered in the regional hospital. Patients who randomise for standard care are thus not burdened with referral to a neurosurgical expertise centre and neurosurgical counselling. Although a greater appeal on regional networks is made, the pragmatic design of PRolaCT intends to lower the threshold for randomisation.

The study intervention in PRolaCT is thus the neurosurgical counselling rather than surgical intervention, which allows patients in the intervention groups to opt for surgery. If there is a substantial proportion of patients in the intervention group who do not undergo surgery, it would lead to an attenuation of found effects. Furthermore, as a part of standard care, participants in the control groups may still undergo surgery in the follow-up of the study (which is sporadically needed in case of severe DA intolerance or resistance). The expected cross-over between treatments was taken into account for the sample size calculation, resulting in a larger sample size needed. However, we anticipate that neurosurgical counselling greatly contributes to patients’ decision for a specific treatment, and therefore, our approach may decrease the risk of study drop-out due to disappointment over the outcome of randomisation.

### Strong patient preference

In our experience, many prolactinoma patients are willing to undergo surgery, which was confirmed by a recent survey conducted by the Dutch Pituitary Foundation. Nonetheless, patients’ willingness to be randomised appears diminished due to a strong preference for a specific treatment, which was generally, but not exclusively, for surgical resection, and patient recruitment has thus far been limited. To overcome this impaired patient recruitment, PRolaCT-O primarily aims to compare HRQoL, remission rates, and cost-effectiveness of neurosurgical and medical prolactinoma treatment in patients who are eligible to participate in one of the RCTs, but refuse randomisation.

The non-interventional nature of PRolaCT-O has some limitations, mainly based on the assumption that all confounders are known and adequately measured. For PRolaCT-O, confounding by indication can be expected, but comprehensive baseline measurements, including exploration of patients’ and physicians’ motivation for a specific treatment choice, may allow for correction for expected confounders, such as the expected likelihood of complete resection, the effectiveness of previous DA treatment, or the amount and severity of side effects to DA treatment at study baseline. Nonetheless, reviews comparing observational studies and RCTs have found effect estimate differences, although not all statistically significant, even when correction for confounding by propensity scoring was used [47, 48]. However, these differences may as well be explained by varying outcome definitions, differentially distributed effect modifiers in the underlying population, when estimates of population-averaged effects are used, and bias in both RCTs and observational studies. Therefore, found differences between effect estimates of observational and randomised studies do not necessarily mean observational studies are less reliable [49]. Clearly, PRolaCT-O cannot replace the randomised studies that are and will remain the mainstay of PRolaCT. However, PRolaCT-O, which aims to have a lower patient threshold for participation, might be more easily implemented in clinical practice, and we believe will provide study results earlier than the RCTs.

Collection of “real-world” data with PRolaCT-O might provide interesting insights in patient characteristics (e.g. presence and severity of symptoms or side effects, prolactinoma characteristics), which may be used for clinical decision-making, facilitating more individually tailored practice of evidence-based medicine.

